## Abstract

**Introduction:**

Excess free sugar intake is associated with obesity and poor dental health. Adolescents consume substantially more free sugar than is recommended. National (UK) School Food Standards (SFS) are in place but are not mandatory in all schools, and their impact on the diets of secondary school pupils is unknown. We aim to evaluate how SFS and wider healthy eating recommendations (from the national School Food Plan (SFP)) are implemented in secondary schools and how they influence pupils’ diets and dental health.

**Methods and analysis:**

Secondary-level academies/free schools in the West Midlands, UK were divided into two groups: SFS mandated and SFS non-mandated. Using propensity scores to guide sampling, we aim to recruit 22 schools in each group. We will compare data on school food provision and sales, school food culture and environment, and the food curriculum from each group, collected through: school staff, governor, pupil, parent surveys; school documents; and observation. We will explore the implementation level for the SFS requirements and SFP recommendations and develop a school food typology. We aim to recruit 1980 pupils aged 11–15 years across the 44 schools and collect dietary intake (24-hour recall) and dental health data through self-completion surveys. We will compare free sugar/other dietary intake and dental health across the two SFS groups and across the identified school types. School type will be further characterised in 4–8 case study schools through school staff interviews and pupil focus groups. Evaluation of economic impact will be through a cost-consequence analysis and an exploratory cost–utility analysis.

**Ethics and dissemination:**

Ethical approval was obtained from the University of Birmingham Ethical Review Committee (ERN_18-1738). Findings will be disseminated to key national and local agencies, schools and the public through reports, presentations, the media and open access publications.

**Trial registration number:**

ISRCTN 68757496 (registered 17 October 2019).

Strengths and limitations of this studyThis research fills a gap in the literature by evaluating the impact of national school food policy on the dietary intake of secondary school pupils in the UK.A validated online dietary assessment tool, adapted for use in an ethnically diverse population, will be used with 1980 secondary school pupils across 44 schools.The research will assess variation in the implementation of the School Food Standards, School Food Plan recommendations and other contextual factors across schools.The study design includes qualitative research to provide an in-depth understanding of school food provision, environments and the culture/ethos relating to this.The study aims to compare schools that are mandated with schools that are not mandated to adhere to the School Food Standards. These two groups may differ in other ways, so to improve the comparability of the two groups, a sampling approach based on propensity scores has been conducted.

## Introduction

Excess sugar consumption is a major contributor to increased energy intake/obesity, adverse cardiometabolic health^1^ and poor dental health.^2^ UK adolescents consume three times their recommended amount of total energy intake from free sugars^3^; almost half of 15- year-old individuals have dental caries^2^ and nearly a third have excess weight.^4^ Adolescence is an important time for dietary intervention as it is a key period for establishing dietary patterns,^5^ with greater autonomy over dietary decisions. A large proportion of adolescent dietary intake occurs while at school, making these opportune settings for intervention.

In the UK, a longstanding strategy for improving children’s diet has been nutritional standards for school food. School meal standards were first introduced in 1941, but fell out of favour later in the 20th century. In 2006, following a national school meal review,^6^ national School Food Standards (SFS) were relaunched in England and became a legal requirement for most state schools. In 2015, a Department for Education (DfE) SFS review resulted in substantial changes. For ease of implementation, nutrient-based standards were removed while retaining food-based standards underpinned by a nutrient framework.^7^

In addition to the national SFS, the School Food Plan (SFP) was launched in 2013, providing a wider set of non-statutory recommendations for schools that promote a ‘whole school’ approach to healthy eating.^8^ One central aim was to increase school meal uptake, as higher demand enables better quality meals to be served at a lower cost. Another aim was to provide practical support, advice and information for headteachers to help improve the quality and uptake of their school’s food. In addition to school food provision, the plan addresses how healthy eating can be incorporated within all aspects of school life and the wider community.^9^

Evaluation of the impact of the 2006 SFS on food provision and consumption has been conducted in primary (age 4–11 years) and middle (age 9–12 years) schools in the UK. Pre-SFS and post-SFS implementation comparisons showed improvements in overall dietary intake in pupils aged 4–7 years, but not in those aged 11–12 years.^10–12^ SFS implementation was good in primary schools but less so in middle schools.^10^ Evidence of SFS impact on secondary school pupils’ (aged 11–16 years) dietary intake is more limited. A study in 80 secondary schools compared school food provision in 2011 with that in 2004. They reported improvements in the nutritional content of school-provided food (in particular reduced confectionery availability) and pupils’ lunchtime food consumption, but did not examine total dietary intake.^13^

To date, the impact of the updated SFS or the SFP has not been evaluated. The way in which SFS legislation was introduced in England means that certain school types (including academies and free schools; 70% of secondary schools in England)^14^ that were set up between January 2010 and May 2014 are exempt from this legislation (although they can choose to voluntarily sign up to the standards), whereas schools of these types established before or after these dates are legally required to meet the SFS. This provides an opportunity to examine how a legal requirement to meet the SFS influences schools and their pupils. Given the lack of SFS/SFP evaluation in secondary schools, we aim to investigate their influence in these settings by comparing school food provision, sales, wider school factors related to food, pupil dietary intake and dental health across those mandated and not mandated to adhere to the current SFS. We will also explore variation in the implementation of the SFS and SFP recommendations and their economic impact.

## Methods and analysis

This is an observational, mixed-method design study, consisting of two phases. Phase I involves collecting a variety of data on SFS/SFP implementation, and school and pupil outcomes in the SFS mandated and non-mandated schools. We will compare outcomes across the two groups and develop a typology of schools based on SFS/SFP implementation and wider school contextual factors. In phase II, we will identify a small number of ‘case study’ schools and conduct a qualitative inquiry to further develop the school typology. Furthermore, we will undertake an economic evaluation to assess how the costs and outcomes vary by school type.

### Study setting

The sampling frame comprises secondary phase academies/free schools providing education to children aged 11–16 years and located within 14 Local Authority areas in the West Midlands region, UK. This region has a population of five million (21% of an ethnicity other than white British),^15^ urban, suburban and rural areas and areas of high socioeconomic deprivation.^16^ Other school types and academies that provide specialist alternative education have been excluded.

### Phase I

#### Sampling

To increase the comparability of the two school groups, stratified sampling, based on propensity scores, was used.^17^ We obtained routine data from the DfE on several characteristics for all schools in the sampling frame: Local Authority area; establishment type; urban/rural; total pupil roll size; Income Deprivation Affecting Children Index; inclusion of a sixth form; selective/non-selective admissions policy; religious affiliation/secular; and proportion of: male/female pupils; pupils from Black, Asian and ethnic minority groups; students with English as a foreign language; students eligible for free school meals; and pupils with Special Educational Needs. We developed propensity scores using linear regression with the SFS status of the school (mandated/non-mandated) as the outcome and school characteristics as explanatory variables. Propensity score quartiles were then used to create four groups with subsequent division by SFS status (based on the date they received academy/free school status), resulting in eight distinct sampling groups. Following the random ordering of each group, schools will be invited sequentially to participate, aiming to recruit five or six schools from each group.

Within participating schools, pupils in one class from each of years 7, 9 and 10 (aged 11–12, 13–14 and 14–15 years, respectively) will be invited to take part. Preference will be given to classes not streamed by academic ability or subject to enable participation of classes that are representative of the year group characteristics. There are no pupil exclusion criteria.

#### Sample size calculation

We used data on free sugar intake pre-SFS and post-SFS implementation from the study undertaken in middle schools by Adamson *et al*^10^ to inform our sample size calculation. Assuming an intraclass correlation coefficient of 0.1^18^ and balanced cluster sizes, we estimated that to detect a difference in mean free sugar intake at lunch of 4 g (20 g vs 16 g) between the two school groups, assuming an SD of 11 with 90% power and at 5% significance, we require 990 evaluable participants and 22 clusters (conservatively using schools^19^) in each group (total schools=44; total participants n=1980; cluster size=45).

#### Recruitment

Headteachers will be invited by post and email with a telephone follow-up. In participating schools, a liaison staff member will be identified and a contract, outlining expected commitments from both parties, will be signed. Once data collection is complete, participating schools will receive a school-specific summary report and £300.

At least 7 days prior to pupil data collection, pupils from the three selected classes will receive a participant information pack (comprising pupil and parent information sheets and a parental opt-out consent form). Schools will also be asked to email documents directly to parents. Pupils whose parents do not return a completed opt-out consent form will be invited to take part in the data collection sessions during the school day and asked for their electronic assent for study participation. Parents of pupils in selected classes will be invited to complete a self-administered parent survey (online or paper copy). Both pupils and parents who participate will receive a £5 voucher.

Participating schools will be asked to identify key staff/governors with roles relating to food provision, eating environment, food curriculum, or SFS/SFP implementation. Identified staff will be sent a staff participant information sheet (email/paper copy) and study invitation for a self-administered survey (online or paper format). Recruitment and data collection processes are outlined in the online supplemental file 1.

10.1136/bmjopen-2020-042931.supp1Supplementary data

School and pupil recruitment commenced in October and November 2019, respectively, and was due to be completed in the 2019/2020 academic year. However, due to restrictions in place in England during the COVID-19 pandemic, recruitment and data collection were suspended in March 2020 and will recommence when schools reopen for all pupils to attend. All further data collection activities will be undertaken in accordance with the relevant Department of Health and Social Care and DfE’ health protection guidance.

#### Data collection

##### Data capture on SFS and SFP implementation and the wider school context

A logic model setting out the processes by which the SFS/SFP are assumed to generate pupil health gains has been developed (figure 1). Briefly, we hypothesise that health gain materialises directly via a change in school food consumption and indirectly by curricular and other activities designed to change pupils’ dietary knowledge, attitudes and beliefs that impact on food consumption in and out of school. The extent to which the SFS/SFP achieve these health gains depends on their implementation within a school, which is influenced by key contextual factors (eg, school management, parental engagement and so on).

**Figure 1 F1:**
[figure not shown]
Logic model and theory of change for the influence of School Food Standards on children’s dietary intake and health outcomes.

Our data collection strategy, guided by the principles for process evaluation outlined in the UK Medical Research Council guidance,^20^ will provide data to populate and refine the logic model. This will enable us to assess the extent to which the SFS requirements and SFP recommendations are embedded in each school and the relative importance of contextual factors in influencing this. Our data collection methods include: school menu analysis; observation of school food provision and the related environment; school document review; collection of aggregated routine data on pupil characteristics; and self-administered surveys for staff, governors, pupils and parents.

##### Assessment of SFS compliance and SFP recommendations implementation

SFS compliance assessment is based on the national SFS checklists for school lunch and school food other than lunch^21^ that consist of daily, weekly and three-weekly criteria for food and drink offered. Using an observation tool developed to measure compliance with the SFS daily criteria, trained researchers will record food and drink provision at all eating occasions across one school day, and at all school food outlets and dining areas. Compliance with the SFS weekly and three-weekly criteria will be assessed from schools’ weekly menus.

Implementation of the SFP recommendations is based on three guidance documents produced by the DfE: (1) a headteacher checklist; (2) a guide to creating a culture and ethos of healthy eating; and (3) guidance for governors.^22–24^ Implementation will be assessed through questions in the surveys to pupils, parents, staff and governors; researcher observation of food outlets and dining areas; and school document review, for example, school food policy, catering contract, curriculum documents and minutes of the Board of Governors and School Council meetings.

The school staff and governor surveys include a series of questions based on Normalisation Process Theory (NPT),^25^ to explore the implementation and sustained embedding of the SFS/SFP. The items in the NoMAD instrument (developed to assess the four NPT constructs)^26^ were adapted for relevance to the SFS/SFP and the school setting.

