#### Data analysis

##### Preliminary development of a school typology

Using the logic model (figure 1) as a guide, we will use data captured on SFS/SFP implementation and the school context to develop an initial typology of schools, which will reflect the degree of implementation of the SFS/SFP and other relevant local initiatives relating to food and healthy eating.

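### One observed school day per school shows whether a daily School Food Standards criterion was met that day, not whether the school complies with it

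*Protocol article*

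**What the plan says.** The section on assessment of SFS compliance bases the assessment on national checklists "that consist of daily, weekly and three-weekly criteria for food and drink offered". It then divides the work by period.

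- **Daily criteria.** "Using an observation tool developed to measure compliance with the SFS daily criteria", the article says, "trained researchers will record food and drink provision at all eating occasions across one school day", "and at all school food outlets and dining areas". Coverage within the day is thorough, but no second day is described, and this section names no other source for the daily criteria.
- **Weekly and three-weekly criteria.** "Compliance with the SFS weekly and three-weekly criteria will be assessed from schools’ weekly menus".

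Under the preliminary development of a school typology, the plan is to "develop an initial typology of schools, which will reflect the degree of implementation of the SFS/SFP", together with other local food initiatives. The inputs are broad. The text after Figure 1 lists "school menu analysis; observation of school food provision and the related environment; school document review", followed by routine pupil data and surveys.

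Under analysis of pupil outcomes, the main comparison is between mandated and non-mandated schools. Models relating school type to pupil outcomes are described as exploratory.

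**The concern.** The natural reading of a daily criterion is a rule that applies on each school day. One visit samples a single day from the period the rule covers. It cannot separate a school that always meets the criterion from one that usually does. It also gives no estimate of how much provision varies from day to day within a school.

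The errors run one way. If the observer records correctly, a school that always meets the criterion cannot fail, while one that meets it on most days can pass. A statement that a school complies with a daily criterion would therefore tend to be too favourable.

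This matters because the level of SFS implementation is a stated aim of the study, and the data are meant to show how far the standards are embedded in individual schools. Averaging over 44 schools does not help a statement about one school. Misplaced schools could also weaken the exploratory associations between school type and pupil outcomes.

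**Working it through.** **Inputs.** From the article: one observed day per school for the daily criteria, menus for the longer-period criteria, and 44 schools. The article gives no number of daily criteria, no day-to-day variance, no pass/fail rule and no typology weights. There is no figure of its own to reproduce here, so everything below rests on assumed ranges.

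**1. One criterion, one school.** Let p be the share of school days on which the criterion is met, and let the visit fall on a typical day. Then P(met on the observed day) = p. With independent days, P(met on all k days) = p^k.

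| p | Met on the observed day | Met on all 5 days, p^5 | Difference |
|---|---|---|---|
| 0.80 | 0.80 | 0.33 | 0.47 |
| 0.90 | 0.90 | 0.59 | 0.31 |
| 0.95 | 0.95 | 0.77 | 0.18 |

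The size depends on independence; the direction does not. Meeting a criterion on every day implies meeting it on the observed day, so the one-day pass rate cannot fall below the all-days rate. If a school's days are nearly identical, the difference approaches zero.

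**2. Several criteria at once.** If a school passes only when every criterion is met, false passes become rarer. With p = 0.9 and independent criteria, the chance of passing all of them on one day is 0.9^5 = 0.59 for five criteria and 0.9^10 = 0.35 for ten.

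**3. Reliability of a school-level score.** For k days, reliability = k·ICC / (1 + (k − 1)·ICC), where ICC is the between-school share of single-day variance.

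| ICC | 1 day | 5 days |
|---|---|---|
| 0.2 | 0.20 | 0.56 |
| 0.5 | 0.50 | 0.83 |
| 0.8 | 0.80 | 0.95 |

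For a one-day score averaged over m criteria, let r be the per-criterion ICC, rho the correlation of school effects between criteria, and c the correlation of day noise between criteria:

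reliability = r(1 + (m − 1)rho) / [r(1 + (m − 1)rho) + (1 − r)(1 + (m − 1)c)].

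With m = 10:

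- r = 0.2, rho = 0, c = 0.3: 0.20 / (0.20 + 0.8 × 3.7) = 0.06
- r = 0.4, rho = 0.3, c = 0.3: 1.48 / (1.48 + 0.6 × 3.7) = 0.40
- r = 0.4, rho = 0.3, c = 0: 1.48 / (1.48 + 0.6) = 0.71
- r = 0.6, rho = 0.6, c = 0: 3.84 / (3.84 + 0.4) = 0.91

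The answer falls on either side of 0.5, and nothing in the article narrows it.

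**4. The gap between school groups.** At 95% v 85% of days, one day shows a 10-point gap; meeting the criterion on all five days shows 0.774 − 0.444 = 33 points. At 50% v 30%, one day shows 20 points and all five days 0.031 − 0.002 = 3 points. At 80% v 70%, one day shows 10 points and all fifteen days of a three-week cycle 0.035 − 0.005 = 3 points. There is no general direction.

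**The case against.** The case for the plan is substantial.

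- Direct observation records what was actually on offer, which a menu does not. If visit days are typical, the observed-day result is an unbiased estimate of the share of days on which a criterion is met. That is a legitimate quantity for comparing groups. Treating met on all days as the target is a reading of the word daily, since the checklist is not shown. This stands, and it is why the point concerns claims of full compliance rather than observation as such.
- No pass/fail rule is stated, and a condensed article may leave scoring detail to the full protocol. This also stands. The single day, however, is fixed here, and the observation tool is described as measuring compliance.
- Sales data for restricted items over two months add evidence beyond one day. They are weekly aggregates, though, and are not assigned to scoring the daily criteria.
- Menus show planned provision, and the article does not say that they list it by day. Menu scoring could therefore miss departures from plan and could raise apparent compliance. This limits the remedy: menu results belong beside the observed day, not in its place.

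A reader might infer that the school-level score is mostly day-to-day noise, or that many schools would be ranked wrongly. The documents do not support either. Reliability runs from 0.06 to 0.91 under the assumptions tried. No ranking is planned, and the typology draws on menus, documents, surveys and context data as well as the observed day.

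**Conclusion.** The point holds in a limited form. One observed day supports the statement that a daily criterion was met on that day. It does not support a claim of compliance on every school day. For a single criterion, such a claim is biased upward: a school meeting it on 80% to 95% of days passes with probability 0.80 to 0.95, against 0.33 to 0.77 for a full week. Those figures assume independent days, a typical visit day, and that a daily criterion is a rule for each day.

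The effect on a school-level score cannot be sized from the article. A reader might also infer that one-day scoring shrinks the difference in compliance between mandated and non-mandated schools. It does so at some adherence levels and does the opposite at others, so that inference fails.

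The primary comparison is unaffected, because it uses legal SFS status and no compliance score. The consequence is confined to the description of SFS compliance and the exploratory typology analyses. This is an inexpensive improvement to the measurement of a stated aim.

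**What to change.** In the section on assessment of SFS compliance, and in the typology section:

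1. For daily criteria that a menu can show, also score each day of the menus already being obtained. Give both the share of days met and whether the criterion was met on all days. Report this as planned provision beside the observed-day result, and check one against the other.
2. For daily criteria that only observation can show, report them as met on the observed day, not as compliant.
3. Use both the menu-based and the observed-day scores as typology inputs.

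The cost is some extra menu coding and a change of wording, with no additional visits. The downside is that menus show planned rather than actual provision and cover only part of the daily checklist. If a school's menus do not list provision by day, step 1 is not possible for that school, and step 2 applies to all its daily criteria.
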